#### Patient factors

Age, sex, comorbidities (history of ischemic heart disease, cerebrovascular disease, diabetes mellitus, previous abdominal surgery, Body Mass Index (BMI) >30, smoking) nutritional status (measured as Nutritional Risk Score (NRS) [30] and serum albumin levels, use of oral anticoagulants, use of immunosuppressive medication, anaemia (measured based on preoperative haemoglobin levels), insurance class.

#### Procedural factors

Indication for surgery (malignancy (and UICC stage), inflammatory bowel disease, other), urgency (elective (planned)/expedited (within two weeks of decision to operate)/emergency (unplanned)) bowel preparation, antibiotic decontamination, primary and secondary operating surgeon (staff grade, specialization, yearly colorectal case load of responsible surgeon (lead or instructor)) and whether procedure was performed as a teaching procedure, operative approach (open, laparoscopic, robotic, converted), operative field contamination (clean-contaminated/contaminated/dirty), anastomosis formed (stapled/hand sewn/no anastomosis (end colostomy formation)/protective diversion) anastomotic configuration (side-to-side/end-to-side/end-to-end), anastomotic test performed (air leak test, endoscopy), result of test (leak/no leak), consequence of test (revision, oversewing, stoma formation).

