## 3. Interventions

### 3.1 Intervention description

During the control period, patients are treated according to their local standard of the contributing hospitals. During this period no special interventions are planned, but baseline data will be obtained. Data according to the CRF will be collected for the pre-, intra-, and postoperative course, including all complications according to the Clavien Dindo Classification [28] for each complication to calculate the primary outcome measure (CCI) [27].

After the control period the full CB is implemented during a period of 1 month in every contributing hospital.

The CB will consist of the following items:

Preoperative optimization of the nutritional status: Perform Nutritional Risk Score (NRS), measure albumin or prealbumin preoperatively and initiate nutritional support and delay surgery by at least two weeks if clinically feasible to allow improvement of nutritional status in case the NRS is >2.Preoperative showering with an antiseptic agent on the night before or the day of admission for all patients.Antibiotic decontamination (which is optional according to institutional preference) and mechanical bowel preparation (for all).Administer preoperative antibiotic prophylaxis within 60 minutes prior to skin incision (not after and not any earlier).Hair removal in the operative field with clippers (no shaving).Peri-, intra-, and postoperative warming to maintain body temperature above 36 °C and peri-, intra- and postoperative glucose control below 9 mmol/l until patient leaves the wake-up area.Usage of a wound protection device (such as Alexis® wound protector or others).Change of gloves and instruments after anastomosis respectively the contaminated phase in patients with end colostomy formation.Anastomosis only with experienced senior surgeon present in the operating theatre for any elective and emergency procedures (senior surgeon will be defined as follows: “Schwerpunkt Träger Viszeralchirurgie” and/or “European Board of Surgical Qualification (EBSQ) Colorectal”, and/or certified operator according to Deutsche Krebs Gesellschaft (DKG) alternatively a head of department/local principal investigator can name surgeons in case of other qualification if deemed necessary).

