### 3.7 Sample size

The sample size calculation described below is for an observational study. Simulations were used to estimate the required sample size. Specifically, we generated 1111 synthetic datasets for a range of potential sample sizes and possible reductions in CCI score due to the modified standard. We then applied the intended analysis (a linear mixed effects model with CCI as the outcome) to each of the simulated datasets. We modelled adoption of the modified standard as a fixed effect and the surgery performance of each study centre as a random effect to account for expected variation in outcomes.

The simulations are based on the following assumptions.

The modified standard will be studied in eight middle sized centres (Clarunis Site Universitätsspital Basel, Kantonsspital Aarau, Spitalzentrum Biel, Kantonsspital Baselland, Luzerner Kantonsspital, Spital Limmattal, Kantonsspital Olten and Lindenhofspital Bern) and one large centre (Clarunis Site St. Claraspital).

We assume that each middle size centre contributes n patients to each condition under study (before and after adoption of the CB) and that Clarunis Site St. Claraspital contributes 2 × n patients to each study condition.

The average CCI score pre-modified standard is 30 with a standard deviation of 12.5 [27].

The standard deviation for surgery outcomes among the centres under study is 20 (based on mortality data from the participating study centres provided by the Swiss Federal Office of Public Health) [8].

We assess the change in CCI using a linear mixed model with CCI after 30 days as the outcome variable, CB implementation as a binary factor and study centre as a random effect. The hypotheses are tested applying a one-sided Wald test for the regression coefficient estimated for the CB factor at the 2.5% Level and a target power of 90%.

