Assuming that the CB improves CCI scores by 10 points, 5 patients are needed for each study condition from each middle-sized study centre and 10 patients for each study condition from St. Claraspital. Thus, at least 10 patients should be recruited from each small study centre and 20 patients from St. Claraspital for a combined total sample of 90 patients. This sample size allows detection of an improvement on the CCI with 90% probability (power), assuming that the CB really does reduce the CCI by 10 points on average. As the study is not randomized, the models will include all potential confounders of the true association between the intervention and the outcomes in the final models. To accurately estimate this association the sample size needs to be increased by a variance inflation factor (VIF) that reflects the correlation between the intervention and the confounding factors [29]. As this is difficult to quantify, a conservative VIF of 3.3 was applied to the estimated sample size so that a total of 149 patients per arm and a total of 298 for the study. This target sample size can be realistically achieved within the study period based on current estimated caseloads in the contributing hospitals. This power calculation was performed by the statistical department of the Clinical Trial Unit (CTU) of the Department for Clinical Research of the University Basel and reviewed by an independent statistician. The CTU is a well-established and validated unit. The secondary endpoints as described above will be analysed using descriptive statistics.

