### 4.3 Statistical methods

The primary objective of the study is to be measured by the CCI 30 days post-operative compared to the CCI under standard care as the control group. The average CCI of patients treated in participating hospitals before implementation of the CB will be compared with the average CCI after implementation.

We hypothesize that the CB will be effective in reducing CCI scores 30 days post-operation as compared to standard care.

H0: The average CCI of patients treated after implementation of the CB is the same as (or higher than) the average CCI before implementation.H1: The average CCI of patients treated after implementation of the CB is lower than the average CCI before implementation.

The analysis of the primary and secondary outcomes will be made based on a one-sided Fisher`s Exact Test with the assumption of an alpha level of p < 0.05 to be considered significant. A multivariable analysis will be performed to control for the above-mentioned confounding factors concerning the primary endpoint.

For adjusted analyses, the following potential confounding factors are accounted:

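### The adjusted primary model treats two bundle components and the intra-operative leak-test results as confounders, so its bundle coefficient is not the total effect the protocol sets out to estimate

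*Protocol article*

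**What the plan says.** The target is a total effect. Section 4.3 states: "The average CCI of patients treated in participating hospitals before implementation of the CB will be compared with the average CCI after implementation". Section 3.7 describes the model as having "CB implementation as a binary factor and study centre as a random effect". The exposure is therefore the bundle as a whole, not its items one by one.

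The adjustment is meant for that same comparison. Section 3.7 says that, because the study is not randomised, "the models will include all potential confounders of the true association between the intervention and the outcomes in the final models". Section 4.3 ties the multivariable analysis to the primary endpoint and opens the list with "For adjusted analyses, the following potential confounding factors are accounted".

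Under Procedural factors the list contains "bowel preparation, antibiotic decontamination, primary and secondary operating surgeon (staff grade, specialization" and later "result of test (leak/no leak), consequence of test (revision, oversewing, stoma formation". Section 3.1 gives as one of the nine bundle items: "Antibiotic decontamination (which is optional according to institutional preference) and mechanical bowel preparation (for all".

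**The concern.** A component of an exposure cannot confound the effect of that exposure. Once a regression holds bowel preparation fixed, the CB coefficient compares periods among patients with the same bowel preparation, and the gain from introducing it is credited to the covariate. The same holds for decontamination in any hospital that adopts it with the bundle. A leak-test result, and the revision, oversewing or stoma that follows it, comes after the preoperative items and may be one of the ways in which they change the outcome.

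At stake is the answer to the primary question. In an unrandomised before-after study the adjusted estimate is the one readers will rely on, and a bundle that works could be reported as having little effect.

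**Working it through.** **1. The passages side by side.**

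| Variable on the adjustment list | Status under section 3.1 | Relation to the bundle |
|---|---|---|
| Bowel preparation | Bundle item, for every patient | Component |
| Antibiotic decontamination | Bundle item, optional by hospital | Component where newly adopted |
| Leak-test result and consequence | Not an item; arises during the operation | After the preoperative items |

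The Introduction states that bowel preparation with decontamination has reduced SSI in randomised trials and leakage in cohort studies. By the protocol's own premise, the two components lie on the path from CB to CCI.

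**2. The protocol's sample size.** Section 3.7 starts from 90 patients, 45 per arm, and applies a VIF of 3.3: 45 × 3.3 = 148.5, so 149 per arm and 298 in total. This step reproduces. The base of 90 does not: the stated layout gives 8 × 10 + 20 = 100. That is a separate matter, and nothing below depends on it.

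**3. What the VIF covers.** VIF = 1/(1 − R²), so 3.3 implies R² = 1 − 1/3.3 = 0.70 between the CB factor and the covariates. It allows for a larger standard error. It does nothing about a coefficient that targets the wrong quantity.

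**4. Illustrative attenuation.** The share s of the effect carried by the adjusted variables is an assumption; the protocol gives none. The coefficient then targets 10 × (1 − s).

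Inputs from section 3.7: SD 12.5, one-sided 2.5%, 149 per arm, VIF 3.3. Effective n per arm = 149/3.3 = 45.2. SE = 12.5 × √(2/45.2) = 2.63. Power = Φ(target/2.63 − 1.96).

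| s | Target (points) | Power |
|---|---|---|
| 0% | 10 | 97% |
| 25% | 7.5 | 81% |
| 50% | 5 | 48% |
| 75% | 2.5 | 16% |

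A simulation (149 per arm, component use 50% before and 95% after, both assumed) confirms the attenuation. The unadjusted estimate averaged −9.9 to −10.0; the adjusted one averaged −7.4 at a 25% share and −5.0 at 50%.

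**5. Precision.** Assume that all patients have bowel preparation under CB and a fraction p had it before, with equal period sizes. Then φ² = ((1 − p)/2)² / (m(1 − m)) with m = (1 + p)/2, and VIF = 1/(1 − φ²). For p = 10, 20, 30 and 50% the VIF from this one covariate is 5.5, 3.0, 2.2 and 1.5. Only the first exceeds the whole allowance of 3.3, though the other covariates must share that allowance.

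**The case against.** **The list may serve the risk-factor objective in section 1.1.** It could, but section 4.3 attaches it to the primary endpoint, and section 3.7 puts confounders of the intervention effect into the final models.

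**The unadjusted comparison is untouched, and the model in section 3.7 names only CB and centre.** Both are true. But the only unadjusted test in section 4.3 is Fisher's exact test, which does not suit a continuous CCI, and the sample was inflated precisely so that the adjusted model could be used.

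**Decontamination is optional, withheld in emergency and expedited surgery (section 3.4), and has its own objective.** This stands in part: where practice is the same in both periods, no bundle effect runs through it. Bowel preparation is not affected by this argument.

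**Some procedural variables also reflect case mix.** This stands. Anastomosis versus end colostomy is an example, and dropping it may leave confounding.

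**The power figures assume that recruitment stops at 298.** This also stands. The caseloads in section 2.1 sum to 1,415 a year, about 707 per period. If half were enrolled (an assumption), there would be about 354 per arm, or 107 effective. SE = 12.5 × √(2/107) = 1.71, and power for a 5-point target is Φ(5/1.71 − 1.96), about 83%. The attenuation itself does not shrink with sample size.

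Four stronger readings are tempting but unsupported:
- *NRS and albumin necessarily carry the nutrition item's effect because preoperative parameters are recorded on day −1.* Section 3.1 has them measured first, with the score then triggering support. Table 1 does not say which value enters the model.
- *Surgeon qualification is itself a bundle item.* The item is a senior surgeon's presence in theatre; grade and specialisation of the operating surgeons are a proxy.
- *End-colostomy patients would be dropped from the model.* No complete-case rule is stated, and the list has a no-anastomosis level.
- *CB and bowel preparation are nearly collinear.* That holds only if earlier use was low, and the protocol gives no figure.

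**Conclusion.** The point holds for mechanical bowel preparation, for antibiotic decontamination where it is adopted with the bundle, and for the leak-test result and its consequence. Followed as written, the adjusted model yields a CB coefficient that excludes the effect passing through these variables, whereas the stated objective is the effect of the whole bundle. The contradiction is explicit in the protocol and is not a detail left to an analysis plan.

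The direction is towards no effect provided the components work as the Introduction says; the leak-test variables could push it otherwise. The size is unknown. The 7.5, 5 and 2.5 points rest on assumed shares, and the power figures also on 298 patients and a VIF of 3.3. A reader might infer that every procedural factor is a mediator or that the study is bound to be underpowered; the protocol supports neither.

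**What to change.** Divide the list in section 4.3 into three groups.

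1. **Primary CB-effect model:** centre, plus factors fixed before the bundle acts. These are age, sex, comorbidities, BMI, smoking, medication, haemoglobin, insurance class, indication and stage. Add urgency as classified at the decision to operate, because the nutrition item's delay could shift the expedited class. Add NRS and albumin, specified as the first screening value before any nutritional support.
2. **Removed from that model:** bowel preparation, antibiotic decontamination, and leak test performed, result and consequence. Use them only for the risk-factor and decontamination objectives in section 1.1.
3. **Labelled sensitivity analysis:** surgeon grade, specialisation and case load, teaching status, operative approach including conversion, field contamination, and anastomosis type and configuration. The bundle may affect these, but some may also reflect case mix.

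The cost is a change of wording in the protocol and analysis plan. The downside is that some case-mix confounding may remain in the primary model; the sensitivity analysis would show how much the estimate depends on it. Precision could move either way, since some of the variables left out may predict CCI well.

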## 5. Methods: Monitoring

### 5.1 Data monitoring

The Clinical Trial Unit (CTU) of the University Hospital Basel conducts the study-specific monitoring. The monitor periodically verifies the conduct of the study and data collection to ensure that all activities are carried out according to the protocol and that data quality and documentation in the electronic case report forms (eCRF) is accurate and complete. All source data and project related files and documents are accessible to the monitor and questions are discussed during the monitoring visits.

## 6. Ethics and dissemination

### 6.1 Protocol amendments

Substantial changes to the project set-up, the protocol and relevant project documents will be submitted to the Ethics Committee for approval according to HRO Art. 18 before implementation. Exceptions are measures that have to be taken immediately in order to protect the participants.

### 6.2 Consent or assent

General consent will be obtained according to the local hospital protocols at admission, or in case of expedited emergency admission during the course of treatment. Depending on the center, the general consent is either collected by specialized study nurses or the responsible study physicians. The Study was approved by the local ethic committee “EKNZ” (Ethikkomission Nordwest-und Zentralschweiz) on 07/09/2020 (Project-ID: 2020-01494).

### 6.3 Confidentiality

Project data is handled with uttermost discretion and is only accessible to authorized personnel who require the data to fulfil their duties within the scope of the research project. On the CRF and other project specific documents, participants are only identified by a unique participant number.

Treating institutions and physicians are reversibly anonymized within the database as well. There is no unblinded interinstitutional benchmarking. Data will not be published with identifiable information on the individual contributing hospitals or physicians.

### 6.4 Access to data

The final trial dataset will only be accessible for the PI and two co-PIs as well as the dedicated study statistician.

### 6.5 Dissemination policy

Publication of this study, data sharing or raw data access is only permitted with direct permission of the sponsor-investigator and all Co PIs. Publication of the main trial will be performed under a group authorship of all contributing hospitals (e.g. “Basel Colorectal Working Group”) and their Co PI and co-workers. Side arm projects will be performed and published based on the individual contribution to each project. Projects will be assigned within regular meetings of the PI and Co PI to individual contributing institutions. Participant level data and statistical code cannot be made accessible currently.

## 7. Discussion

The improvement of outcomes and reduction of complications in colorectal surgery is a highly relevant topic for patients and providers. A high rate of up to 40% of patients suffer from major complications after colorectal cancer surgery [7]. In these cases, surgical complications like anastomotic leakage will potentially lead to a worsened oncological outcome and lead to delay or even cancellation of adjuvant therapies [8]. The intended introduction of a CB to reduce postoperative complications has the potential to reduce these sometimes-life-threatening complications which is in the best interest of all patients undergoing colorectal surgery. The joint introduction of such quality improvement measures in an entire health care region like in the north western part of Switzerland allows a good generalizability of results from our study. There have been only few attempts to minimize the perioperative complication rate in colorectal surgery by introduction of standardized protocols that regulate the perioperative treatment. Studies of the past showed that standardization of these processes can lead to a reduction in postoperative complication rate, like it was shown for the introduction of the Enhanced Recovery After Surgery Protocol (ERAS) [31]. Some of the items from the colorectal bundle have also been included in the ERAS guidelines from 2018. These are preoperative nutritional care, administration of antibiotic prophylaxis 60 minutes before the procedure, antiseptic showering, bowel preparation and preventing of intraoperative hypothermia [13]. Other items such as changing gloves after the contaminated phase, presence of senior surgeon at formation of the anastomosis, antibiotic decontamination and shaving with clippers have not yet been included in the ERAS guidelines. Despite the parallels, the implementation of the ERAS Guidelines in the individual hospitals is sometimes variable. The simultaneous and binding introduction of a firmly defined treatment plan in an entire health region will help to uncover synergistic effects of the individual items and thus help to further scientifically substantiate the use of these items in the ERAS program.

There is another ongoing study of the European Society of Coloproctology investigating a quality control improvement program for right sided colorectal resections and anastomosis. To get a comprehensive picture of the treatment of these patients, we will use synergies to this EAGLE Trial [32].

We choose to use the CCI as the primary endpoint as it offers a modern and unique tool to measure and quantify the impact of all complications that happen to a given patient. It will best reflect their burden for patients and providers [9]. As a continuous parameter it allows to detect clinically relevant results with a lower sample size than for other purely event driven and therefore rarer endpoints such as mortality or anastomotic leakage [9]. By pooling the data from nine different institutions we are able to gain the target power within a reasonable amount of time (6 months for control and modified standard each).

